### Consequences of an absent diagnostic instrument for an early diagnosis in wheezing children

In current clinical practice, the absence of a proper diagnostic test for an early asthma diagnosis in young children leads to at least 2 major health problems: 1) children with asthma are frequently underdiagnosed and undertreated; 2) children with transient wheeze are often overtreated with asthma medication.

Considerable underdiagnosis and undertreatment occurs in young children with asthma [16]. Preschool children with asthma and more severe symptoms (having asthma-like symptoms more than twice per week) benefit from maintenance treatment with inhaled corticosteroids (ICS). This improves symptoms, lung function, quality of life, and reduces exacerbation rate and hospital admissions [1]. As a consequence of undertreatment, more children will suffer from uncontrolled asthma with more exacerbations, emergency care visits, hospital admissions, and in the long run even airway remodelling and permanent loss of lung function [17]. Therefore, this undertreatment may lead to reduced quality of life and increased direct and indirect medical costs.

Overtreatment of children with transient wheeze occurs with an increased risk of side effects of ICS and bronchodilators such as reduced linear growth, tremor, and palpitations [1, 16]. Treatment with bronchodilators or ICS might not be very effective in children with viral wheeze, which leads to preventable costs of care and preventable side-effects [1, 17, 18]. Moreover, because of uncertainty of the parents and the primary care physicians, a lot of children with transient wheeze are referred to secondary or tertiary care centres, with additional examinations such as chest X-rays, allergy tests, and treatment with asthma drugs as a consequence.

Therefore, a predictive instrument for an early asthma diagnosis will be of great importance to improve treatment of and care for the large group of young children with wheezing symptoms, and will probably lead to a substantial reduction in the cost of care.

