### Inclusion criteria

Wheezing children: age between 2 and 4 years old and presence of two or more objectified (by a physician or nurse) episodes of wheezing and shortness of breathHealthy children: age between 2 and 4 years old

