### Growth

Weight and height will be assessed in height standard deviation (SD) z-scores according to national growth data. Height velocity will be calculated.

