### Asthma or transient wheeze diagnosis at 6 years

The final diagnosis of transient wheeze or asthma will be made by two paediatric pulmonologists after the clinical visit at the age of 6 years. These paediatric pulmonologists will be blinded for the probability diagnosis (if applicable) of the participants. The asthma diagnostic algorithm for children as published by the ERS taskforce in 2021 [38] will be used to establish this final diagnosis. A diagnosis of asthma is made in children with symptoms of asthma when at least two out of the following objective test results are abnormal: spirometry, BDR or FeNO. With respect to spirometry, an FEV_1_/FVC ≤ the lower limit of normal (LLN) or ≤ 80%, ór an FEV_1_ ≤ LLN or ≤ 80% of predicted should be considered abnormal. If this is the case, BDR testing will be performed and an increase in FEV_1_ of more than 12% and/or more than 200 mL following an inhalation of 400 µg salbutamol is considered as an abnormal test result. A FeNO value ≥ 25 ppb should be considered as an abnormal test result. In those patients in which spirometry is normal, but FeNO concentration is higher than 25 ppb, a direct bronchial challenge test using methacholine will be performed. A provocative concentration of methacholine of ≤ 8 ml/mL that results in a 20% drop in FEV_1_ should be considered as a positive test.

Statistical methods

General descriptive statistics will be applied to describe the baseline characteristics. Table 2 depicts the different study groups in which the main statistical analyses will be performed.

**Table 2 Tab2:** outcome parameters and corresponding outcome measures and methods of analysis (see Fig. 5 for corresponding analysis groups)

Outcome	Analysis group	Outcome measure	Methods of analysis

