**Randomised Controlled Trial**			
*Primary*			
Difference in the percentage of well controlled asthma-like symptoms after 1-year follow-up	I	TRACK-score	Unpaired t-test / Mann Whitney-U test
*Secondary*			
Pharmacotherapy	I, II, III, IV	Cumulative ICS dosage (fluticasone equivalent)	Mann Whitney-U test
Growth retardation	I, II, III, IV	SD deviation from target height	Unpaired t-test
Amount of exacerbations	I, II, III, IV	Amount	Chi-square test
Amount of hospital admissions	I, II, III, IV	Amount	Chi-square test
Quality of life child	I, II, III, IV	EQ-5-DY by proxy	Unpaired t-test / Mann Whitney-U test
Quality of life caretaker	I, II, III, IV	EQ-5-DY	Unpaired t-test / Mann Whitney-U test
Lung function (tremoflo)	I, II, III, IV	R_5_, R_5-20_, X_5_, X_5-20_, AX, F_res_ (baseline and % change after salbutamol)	Unpaired t-test / Mann Whitney-U test
Lung function (spirometry)	II, III, IV	FEV_1,_ FVC, MEF50 (baseline and % of change after salbutamol)	Unpaired t-test / Mann Whitney-U test
Absence of school and work (parents)	I, II, III, IV	Number of days	Chi-square test
Healthcare resource use and –costs	I, II, III, IV		Unpaired t-test / Mann Whitney-U test
Costs outside healthcare	I, II, III, IV	Euro	Unpaired t-test / Mann Whitney-U test
Cost-effectiveness	I, II, III, IV	Societal cost per QALY and health care cost per additional child with control of asthma-like symptoms	Sensitivity and bootstrap analysis

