### Assessment of improvement in health gain and costs of care with the application of the breath test in wheezing preschool children

The effect of the intervention will be assessed by comparing the outcome measures between the intervention and the usual care group in the RCT. Dichotomous parameters will be tested with the chi-square test. Continuous variables will be tested for significance with the unpaired t-test for normally distributed parameters and the Mann Whitney-U test in case of a not-normal distribution.

Total treatment costs will be calculated by multiplying resource use with the costs per unit. Resource use (visits to the general practitioner or specialist, emergency visits, hospital admission, lung function tests and other diagnostic procedures, the breath test, (over-the-counter) medication, and lost work days by parents due to sickness of the child) will be obtained from a specially designed questionnaire with a recall period of three months. The parents will fill out this questionnaire at baseline and at 3 months interval during the follow-up. Sources for valuation of the costs will be cost-prices of the Dutch manual for costing and cost-prices from the Dutch pharmacotherapeutic compass [45, 47–49] (reference data 2022). If necessary, local hospital cost-prices will be used, which are largely based on integral cost-prices from the Dutch hospitals [50]. Absence of work reported by the parents will be calculated by using the friction cost method, which is recommended by the Dutch manual for costing [47, 48].

The cost-effectiveness analysis from the healthcare perspective will be based on symptom control according to the TRACK questionnaire at 1 year follow-up (primary outcome measure). The cost-effectiveness analysis from the societal perspective will be based on the EQ-5D-Y. The EQ-5D-Y will be completed at baseline and at 3 months intervals during the follow-up, and will be filled out by one of the parents.

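### Pre-bronchodilator lung function is compared between arms with no adjustment for body size, which costs precision, mainly for oscillometry at one year

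*Protocol article*

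**What the plan says.** Table 2 (Randomised Controlled Trial, secondary outcomes) gives the oscillometry measures as "R_5_, R_5-20_, X_5_, X_5-20_, AX, F_res_ (baseline and % change after salbutamol" and the spirometry measures as "FEV_1,_ FVC, MEF50 (baseline and % of change after salbutamol". Spirometry is done only at the final visit, so 'baseline' in these rows must mean the value before salbutamol. The method in both rows is an unpaired t-test or Mann-Whitney test. The section on health gain and costs of care repeats the rule: "Continuous variables will be tested for significance with the unpaired t-test for normally distributed parameters and the Mann Whitney-U test". No covariate is attached to it.

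The relevant ages and visits are these:
- Inclusion criteria: "age between 2 and 4 years old and presence of two or more objectified". Study setting narrows this to children aged 2 or 3.
- Outcomes: secondary outcomes are compared after one year and at the end of the study, with spirometry at age 6.
- Lung function: oscillometry is annual; spirometry belongs to the age-6 visit.

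Elsewhere the article does allow for body size. Growth states: "Weight and height will be assessed in height standard deviation (SD) z-scores according to national growth data". The growth row of Table 2 is also on an SD scale. The age-6 diagnosis calls an FEV1 at or below "LLN or ≤ 80% of predicted should be considered abnormal".

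The statistical section also announces a multivariable analysis that includes age, level of care, genetic background and region. It names no outcome or model for that analysis, and neither height nor sex is listed.

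**The concern.** Airway resistance, reactance and forced volumes vary with body size. If they are compared as measured, the spread due to size goes into the error term, and a real difference between arms is harder to detect. The article gives lung function a role in both directions. Its background lists, among the consequences of undertreatment, "in the long run even airway remodelling and permanent loss of lung function", and its hypotheses include improved lung function in children who receive an early asthma diagnosis. An insensitive comparison weakens the evidence on both. Table 2 states the measure and the test together, and it standardises growth but not lung function, so this is more than a detail left open.

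**Working it through.** **The plan's own figure.** The two-proportion formula for 20% against 40%, two-sided alpha 0.05, 80% power and continuity correction gives 91 per arm, as stated. Dropout of 10% gives 91/0.9 = 101.1, so 102 per arm or 204 in total; the plan takes 220. After 10% dropout, 220 × 0.9 / 2 = 99 per arm remain. All this concerns the primary outcome. The article gives no SD, effect size or power for lung function.

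**Where the age range acts.** Entry at 2 to 4 years puts the one-year oscillometry at about 3 to 5 years. Spirometry and end-of-study oscillometry take place at age 6, so the entry window does not spread ages there.

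**How much the age range adds to height variance.** Assumed, not from the documents: growth g of 6 to 8 cm/year, height SD s of 3.5 to 5 cm at a fixed age, age uniform over a window of W years. Share of height variance due to age = (gW)²/12 ÷ [(gW)²/12 + s²].
- W = 2, g = 6, s = 5: 12/(12 + 25) = 32%.
- W = 2, g = 8, s = 3.5: 21.3/(21.3 + 12.25) = 64%.
- W = 0 (all seen at the same age): 0%. If age-6 visits spread over a full year (W = 1): about 11% to 30%.

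These are shares of height variance, not of lung-function variance. They show which visit is most exposed.

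**Loss of power.** Let R² be the share of outcome variance explained by body size and age (assumed). Without adjustment the SD is larger by 1/√(1 − R²). With 99 per arm and two-sided alpha 0.05, the adjusted comparison has 80% power at (1.960 + 0.842) × √(2/99) = 0.398 residual SD. Unadjusted power for the same difference is Φ(2.802 × √(1 − R²) − 1.960).

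| R² | Unadjusted power | Detectable difference at 80% power (residual SD) | Sample-size equivalent 1/(1 − R²) |
|---|---|---|---|
| 0 | 80% | 0.40 | 1.00 |
| 0.1 | 76% | 0.42 | 1.11 |
| 0.2 | 71% | 0.45 | 1.25 |
| 0.3 | 65% | 0.48 | 1.43 |
| 0.4 | 58% | 0.51 | 1.67 |
| 0.5 | 51% | 0.56 | 2.00 |

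**The same loss from the other side.** If the unadjusted test has 80% power for 0.4 SD at 99 per arm, removing size-related variance raises it to 86%, 90% and 94% for correlations with body size of 0.4, 0.5 and 0.6 (R² = 0.16, 0.25, 0.36). The 0.4 SD is also an assumption.

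**The case against.** The strongest reply is that the lung-function rows give no units. 'Unstandardised' is therefore inferred from silence, and the article may leave the scale to a fuller document. That stands as a caution. But the article names standardisation where it wants it, in the growth row, the growth section and the diagnostic rule, and it names an unadjusted test here.

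Several further limits also stand:
- A reader might infer that body size swamps the signal across all lung-function outcomes because of the two-year entry range. The documents do not support this. The range bears on one-year oscillometry, not on spirometry or end-of-study oscillometry, and the loss is small if R² is low.
- A reader might infer bias, or false findings from a chance height imbalance. Under randomisation the unadjusted test is unbiased and keeps its nominal error rate. Only precision is lost.
- The percentage change after salbutamol is relative to the child's own value and largely free of size.
- Table 2 lists spirometry for analysis groups II to IV but not I, and the figure defining the groups is not shown. The 99 per arm is therefore not established for spirometry.
- Age is named for the multivariable analysis. If that analysis covered lung function it would recover part of the loss, but the article does not say so and its stated purpose is to explore influences on outcome.

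Adjusting for current height would bring a problem of its own. It is measured after randomisation, the background lists reduced linear growth among the side effects of inhaled corticosteroids, and growth is itself a between-arm outcome. Regression should therefore use baseline covariates.

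**Conclusion.** The point holds as a matter of precision on a secondary outcome. Table 2 pairs pre-bronchodilator oscillometry and spirometry with an unadjusted two-sample test and names neither a size standardisation nor a covariate. The comparison is valid but less sensitive than the data allow, mainly for oscillometry at one year. At 99 per arm, 80% adjusted power corresponds to 76% unadjusted at R² = 0.1, 65% at 0.3 and 51% at 0.5. This rests on an assumed R², on reading the named parameters as unstandardised, and on an alpha of 0.05 before the multiplicity correction that the article mentions. It is a cheap improvement, not a flaw that threatens the trial's main conclusion.

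**What to change.** Change the two lung-function rows of Table 2:
- **Spirometry before salbutamol:** analyse FEV1, FVC and MEF50 as reference z-scores for age, height and sex, and name the reference equations.
- **Oscillometry before salbutamol, at one year and at the end of the study:** compare arms by linear regression with the baseline oscillometry value, baseline age, baseline height and sex as covariates. Where a reference equation exists, z-scores can serve as an alternative or sensitivity analysis.
- **Percentage change after salbutamol:** keep as stated.

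No new measurement is needed, because oscillometry is annual and height is already assessed. There are three downsides. Z-scores depend on the chosen reference equation. They also use current height, which treatment may affect. Some young children will lack a usable baseline oscillometry value, so the plan should say how a missing baseline covariate is handled.

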**Prospective cohort study**			
*Primary*			
Identification of discriminative exhaled VOCs	V	n.a	n.a
Diagnostic value of the VOCs sensing techniques (GC-tof–MS, SIFT-MS) for a diagnosis of asthma or transient wheeze in preschool children*	V	Probability-score > 0.5 is defined as “asthma”	Sn, Sp, true positive and true negative rate
*Secondary*			
Identification of other potential discriminating biological parameters (such as allergic sensitisation, immunological markers, epigenetics, transcriptomics, microbiome) between asthma, transient wheeze, and healthy controls, and the subsequent identification of underlying disease pathways and relation to the discriminative VOCs in the exhaled breath	0, V	n.a	n.a

* based on algorithm

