### A predictive breath test for asthma in preschool children

In 2015 we published the results of a longitudinal study in 202 wheezing children, in which we assessed the potential of exhaled breath biomarkers for a paediatric asthma diagnosis, called the ADEM study (Asthma DEtection and Monitoring study) [22]. In this study, we explored whether clinical parameters, genetic information, inflammatory markers in exhaled breath (such as VOCs), and early lung function measurements assessed at preschool age, could help to predict asthma at age 6 in wheezing preschool children. Our most important finding was that a reliable asthma diagnosis could be established in young children (sensitivity 84%, specificity 82%) by combining clinical information (such as family history of asthma, atopic status and symptoms), and a profile of exhaled VOCs [22]. The addition of 9 most predictive exhaled VOCs to a clinical predictive index, significantly improved an asthma diagnosis (AUC, 89%, an increase of 28% compared to using only the asthma predictive index (API)) which persisted in an external validation set. The chemical identity of these 9 VOCs was determined (see Table 1). This is a promising finding, which demonstrates the proof of principle that exhaled breath biomarkers can be used for an early asthma diagnosis.

**Table 1 Tab1:** the chemical identity of the 9 most predictive VOCs of the ADEM algorithm. BCa 95%CI: Bias Corrected accelerated 95% Confidence Interval [22]

Predicting VOC	Odds ratio	BCa 95% CI	p-value
Acetone	0.93	0.82 to 0.98	< 0.01
Octane	2.91	1.09 to 13.63	< 0.01
2-methylhexane	3.97	1.22 to 126.22	0.01
2,3,6-trimethyloctane	1.51	0.90 to 6.95	0.09
2,6,10-trimethyldodecane	0.98	0.94 to 0.99	0.01
2,4-dimethylpentane	0.79	0.58 to 0.99	0.03
2,4-dimethylheptane	4.25	2.29 to 42.44	< 0.01
2-undecenal	0.08	< 0.01 to 0.53	0.03
2-methylpentane	0.09	< 0.01 to 0.37	< 0.01

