### Hypotheses of the ADEM2 study

The hypothesis of the clinical trial of the ADEM2 study is that application of the breath test in preschool children with asthma-like symptoms will result in important health gain and reduction of costs of care. In children with asthma, we expect that an early diagnosis by the breath test will result in more targeted and better treatment. This will facilitate better asthma control, improved lung function, less exacerbations, less hospital admissions, improved quality of life, and probably less airway remodelling. In children with transient wheeze, we hypothesise that an early diagnosis will diminish uncertainty of parents and treating doctors, with less referrals, less additional examinations (X-rays, allergy tests, microbial cultures or viral PCR tests), and less ineffective treatment (antibiotics, corticosteroids, or antihistamines). Parents will be reassured by the early diagnosis of transient wheeze, which will probably increase quality of life and decrease medical consumption. In both cases, cost savings are expected because of a proper diagnosis by the breath test due to significantly reduced hospital based care and medication use in children with transient wheeze, and prevention of undertreatment related sequela in children with asthma.

Our hypothesis of the observational cohort study with respect to the feasibility, reproducibility and accuracy of the alternative VOC-sensing techniques is that innovative techniques such as SIFT-MS are not inferior to the current golden standard GC–MS. We also hypothesise that new (combinations of) biomarkers will be found that improve the diagnostic accuracy to identify the wheezing preschool child developing asthma, such as epigenetic signatures of blood eosinophils, microbiome data of both nasopharyngeal swabs and faecal samples, whole RNA sequencing on blood, gene-expression of relevant asthma genes, and immunological markers.

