A cost-effectiveness analysis will be performed from a societal and healthcare perspective with a time horizon of 2 years. Incremental cost-effectiveness ratios will be calculated as societal cost per QALY (societal perspective) and health care cost per additional child with control of asthma-like symptoms (healthcare perspective). Standard sensitivity- and bootstrap analysis will be performed to address uncertainty regarding costs and cost-effectiveness outcomes. Cost-effectiveness acceptability curves will be constructed reflecting the probability that the diagnostic breath test is cost-effective for a range of threshold values. Costs and effects after one year will be discounted at 4.0% and 1.5% respectively, according to the Dutch guidelines for health economic evaluation [45, 48].

All outcome parameters and corresponding outcome measures and methods of analysis are listed in Table 2. The large number of patients (*n* = 220) allows better representation of specific subgroups of specific age, background (primary or secondary/tertiary care), genetic predisposition, and geographic area. All these parameters will be measured and included in the multivariable analysis in order to assess possible influences on outcome. Intention-to-treat analyses will be applied. We will execute two subgroup analyses: one for age and one for level of care (first-line versus secondary/tertiary care). Two-sided *p*-values < 0.05 (with correction for multiple testing) will be regarded as statistical significant.

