### Assessment accuracy of the VOC sensing techniques (GC-tof–MS, SIFT-MS)

The primary outcome of the prospective cohort study is assessed in two ways, namely by comparing the VOCs data of the two VOCs-sensing techniques (GC-*tof*–MS and SIFT-MS) at inclusion of all participating children (both wheezing preschool children and healthy controls) to the final diagnosis at six years of age, and by comparing the VOCs-data of the SIFT-MS at the baseline visit to the results of the gold standard (GC-*tof*–MS) at the baseline visit. The sensitivity, specificity, positive predictive value and negative predictive value for a diagnosis of asthma of the two different VOCs sensing techniques (GC-*tof*–MS and SIFT-MS) will be determined with corresponding 95% confidence intervals. Statistical analysis of the volatilome will be performed by current published standards on data analysis for VOCs analysis in breath [51]. The extensive VOCs data derived from the mass spectrometry analyses will be implemented in an algorithm by using mathematical models for analysis of sensor signals (for instance neuronal networks, random forest, support vector machine, or principle component analysis) as described previously [37].

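### Breath-test accuracy against the age-6 diagnosis is planned only at a 0.5 cut of the probability score; an AUC on the uncut score, its paired difference and a calibration check should stand beside it

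*Protocol article*

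**What the plan says.** Table 2 of the Protocol article (prospective cohort study, primary outcomes) gives the outcome measure for the diagnostic value of the VOC techniques as "Probability-score > 0.5 is defined as" asthma. The method of analysis is "Sn, Sp, true positive and true negative rate".

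The section *Assessment accuracy of the VOC sensing techniques* describes the same outcome: "The sensitivity, specificity, positive predictive value and negative predictive value for a diagnosis of asthma of the two different VOCs sensing techniques" "will be determined with corresponding 95% confidence intervals". All four of these measures need a cut.

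The same section plans a second comparison, SIFT-MS data against GC-tof-MS data at baseline, and names neither a cut nor a measure for it.

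*Hypotheses of the ADEM2 study* expects that "innovative techniques such as SIFT-MS are not inferior to the current golden standard" GC-MS. *A predictive breath test for asthma in preschool children* reports the earlier test both as sensitivity 84% and specificity 82% and as "AUC, 89%, an increase of 28% compared to using only the asthma predictive index". Elsewhere AUC appears only for published clinical indices and in the abbreviation list, never as an ADEM2 analysis.

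**The concern.** The algorithm gives each child a continuous score. Cutting it at 0.5 before any accuracy measure is taken has two costs.

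- **Information is lost.** Children scoring 0.51 and 0.99 count the same, so a real difference between the two techniques is harder to see.
- **Discrimination and calibration are mixed.** Two techniques that rank children equally well can show quite different sensitivity and specificity because one score runs higher. The accuracy section leaves the algorithm open (neural networks, random forest, support vector machine), and the outputs of such methods need not share a calibration.

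At stake is how a primary cohort outcome is read: whether SIFT-MS predicts asthma about as well as GC-tof-MS. The planned measures also give nothing to set beside the earlier AUC of 89%, which the article uses to show the gain over the clinical index.

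A smaller defect sits in the same table row. The true positive rate is sensitivity and the true negative rate is specificity, so Table 2 names two quantities twice, while the accuracy section has predictive values in that place.

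**Working it through.** **The plan's own figures.** The only computed figure is the RCT sample size: 20% against 40%, alpha 0.05, power 80%, 91 per group. It reproduces with a continuity correction (82 without). No power is stated for the comparison of techniques, so there is no figure to reproduce for this point.

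**Inputs from the article.** GC-tof-MS AUC 0.89; asthma in about 30% of wheezing preschool children (*Background*); 220 wheezing children, 10% dropout (*Sample size*). 220 × 0.9 = 198, and 0.30 × 198 = 59.4, so roughly 60 with and 138 without asthma.

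**Assumed, not in the article.** Binormal scores with equal variance; SIFT-MS AUC 0.78 or 0.80; correlation between the two scores 0.5 or 0.7; wheezing children only.

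**Calibration, closed form.** Let d = √2 × z(AUC). For AUC 0.89, d = 1.735. A 0.5 cut on a score built for 30% asthma and shifted by s logits lies at t = d/2 + (ln(7/3) − s)/d. Then Sn = Φ(d − t) and Sp = Φ(t).

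- s = 0: t = 0.867 + 0.847/1.735 = 1.356; Sn = Φ(0.379) = 65%, Sp = 91%.
- s = +1 (score runs high): t = 0.867 − 0.153/1.735 = 0.779; Sn = 83%, Sp = 78%.
- s = −1 (score runs low): t = 0.867 + 1.847/1.735 = 1.932; Sn = 42%, Sp = 97%.

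The AUC is 0.89 in all three.

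**Ranking.** For SIFT-MS at AUC 0.80, d = 1.190. At a balanced cut Sn = Sp = Φ(0.595) = 72%, so Sn + Sp − 1 = 0.45. GC-tof-MS running one logit low gives 0.422 + 0.973 − 1 = 0.40, so the worse technique would look better. This needs the particular pairing shown. With SIFT-MS calibrated to 30%, t = 0.595 + 0.847/1.190 = 1.307, Sn = 45%, Sp = 90%, the index is 0.36, and the order is not reversed.

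**Power, simulation.** 1,500 paired datasets per setting, two-sided 0.05, GC-tof-MS AUC 0.89, 30% asthma. The DeLong paired AUC test is set against paired tests on Sn, Sp, Sn + Sp − 1 (J) and overall accuracy (Acc). Under equal AUCs all tests rejected in 5.0% to 5.4% of datasets. Entries are power in %; gain is the AUC test minus the best cut measure, which is Sn for the calibrated cut and Acc for the balanced one.

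| N | SIFT AUC | r | Calibrated: AUC | Sn | Sp | J | Acc | Gain | Balanced: AUC | Acc | Gain |
|---|---|---|---|---|---|---|---|---|---|---|---|
| 198 | 0.80 | 0.5 | 81.1 | 73.7 | 5.1 | 72.0 | 52.7 | 7.4 | 81.3 | 63.7 | 17.6 |
| 198 | 0.80 | 0.7 | 94.9 | 83.9 | 6.1 | 81.3 | 64.8 | 11.0 | 95.6 | 77.9 | 17.7 |
| 198 | 0.78 | 0.5 | 92.8 | 88.4 | 5.9 | 86.5 | 68.3 | 4.4 | 92.6 | 77.4 | 15.2 |
| 198 | 0.78 | 0.7 | 99.0 | 95.7 | 5.2 | 93.6 | 77.5 | 3.3 | 99.0 | 88.0 | 11.0 |
| 220 | 0.80 | 0.5 | 84.7 | 78.7 | 6.1 | 74.8 | 56.0 | 6.0 | 86.1 | 71.2 | 14.9 |
| 220 | 0.80 | 0.7 | 95.5 | 88.1 | 6.3 | 85.5 | 69.1 | 7.4 | 96.5 | 79.9 | 16.6 |
| 220 | 0.78 | 0.5 | 94.3 | 91.3 | 5.1 | 89.1 | 71.3 | 3.0 | 94.0 | 82.9 | 11.1 |
| 220 | 0.78 | 0.7 | 99.7 | 96.9 | 5.3 | 94.2 | 80.3 | 2.8 | 99.6 | 91.0 | 8.6 |

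The simulation error of one power figure near 80% is √(0.8 × 0.2/1,500) = 1 point. With fresh draws the gains came to about 2 to 10 points (calibrated) and 7 to 18 (balanced), in line with the table.

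Specificity has almost no power at the calibrated cut because the two techniques barely differ there (91% against 90%); the difference falls on sensitivity (65% against 45%). At the balanced cut, sensitivity alone has only 25% to 44% power. Which cut measure shows the difference therefore depends on calibration.

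**The case against.** The strongest reply is that measures at the cut match the use of the test. Under *Intervention*, families and doctors receive one of two labels, with different advice for each. A technique whose scores run high does mislabel children at the delivered cut; that is a real fault, and an AUC would hide it. A cut fixed in advance also avoids choosing a flattering threshold afterwards. All of this stands, and it is why the measures at 0.5 should stay.

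Second, the article is condensed and defers volatilome methods to published standards. A reader might infer from "All outcome parameters and corresponding outcome measures and methods of analysis are listed in Table 2" that an AUC is ruled out. The article does not support that: the sentence sits in the RCT health-gain section, and Table 2 itself omits measures planned elsewhere, such as the predictive values. What remains is that a primary cohort outcome has its measure and method stated in two places, and both depend on the cut.

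Third, a reader might infer that a planned test is underpowered by a fixed amount. No between-technique test or margin is named; the accuracy section plans estimates with confidence intervals. The power figures illustrate lost information, and the loss is small in some settings: about 2 to 4 points over sensitivity at SIFT-MS AUC 0.78 with a calibrated cut.

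Fourth, it would be too strong to say that the results cannot be compared with the earlier study. Its sensitivity of 84% and specificity of 82% are the kind of figure planned here; only its AUC has no counterpart. Nor is every SIFT-MS analysis tied to the cut, since the baseline comparison names none.

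**Conclusion.** The point holds as a cheap and worthwhile improvement. It does not show the 0.5 cut to be wrong. For accuracy against the age-6 diagnosis, the article names only measures that depend on the cut, and these cannot separate a technique that ranks children poorly from one that is merely miscalibrated.

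The calibration effect is the firmer part. Given the article's AUC of 0.89 and 30% asthma, it needs only the binormal form and the size of the shift. A one-logit shift spans sensitivity 42% to 83% and specificity 97% to 78% at unchanged discrimination.

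The power gain (about 2 to 10 points with a calibrated cut, 7 to 18 with a balanced one) also rests on the assumed SIFT-MS AUC and correlation. It leaves out the healthy controls whom the accuracy section includes; the analysis group is defined in a figure not shown.

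**What to change.** In Table 2 and in the accuracy section, add beside the measures at 0.5:

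- for each technique, the AUC of the uncut probability score against the age-6 diagnosis, with 95% CI;
- the paired AUC difference between SIFT-MS and GC-tof-MS, with 95% CI (DeLong);
- a calibration intercept and slope for each score.

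Keep sensitivity, specificity and both predictive values at 0.5 for the delivered label. In Table 2, replace the true positive and true negative rates with the positive and negative predictive values, so that the two places agree.

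The cost is a few lines of text and code, because the scores are produced anyway. The downside is one more accuracy measure to report and interpret, and one that is less direct than sensitivity and specificity for a yes/no label.
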